## Methods

### Cultural Adaptation

To address aim 1, before recruitment and study initiation, steps were taken to adapt the CARE-HF intervention content to the rural sociocultural context using some aspects of the ADAPT-ITT (Assessment, Decision, Adaptation, Production, Topical Experts, Integration, Training, and Testing) model [23]. Specifically, qualitative findings from preliminary research in rural patients with HF [8,12] guided the context of problems and potential strategies included in the program materials and telephone intervention sessions. The problems presented during the card sorting task, a component of the sessions, are drawn directly from this preliminary rural research [8,12]. In addition, during the telehealth sessions, veterans’ values and beliefs are assessed and inform the potential strategies identified in the problem-solving process to enhance adherence and tailor the program to the unique needs of each rural veteran.

### Ethical Considerations

This study was approved by the Florida State University Institutional Review Board (protocol STUDY00003764) to collect verbal consent via the telephone according to the principles of the Declaration of Helsinki, with potential participants maintaining the opportunity to opt out of the study. Telephone sessions are recorded to monitor intervention fidelity. However, all participant data are deidentified and stored in accordance with the General Data Protection Regulation Rules to maintain privacy and confidentiality. Veterans enrolled in the study receive compensation in the form of US $20 gift cards to a superstore following each completed data collection point, for up to a total of US $100 in gift cards if the entire study is completed. No identifiable information or images of research participants will be included in research reports. The CARE-HF protocol is registered at ClinicalTrials.gov (NCT05839067).

### Design and Sample

This study includes a repeated-measures, single-group design. Veterans are recruited from Veterans Administration home-based cardiac rehabilitation clinics, cardiology clinics that serve veterans, veterans-based community resource centers, and social media campaigns using study flyers. Veterans with HF (N=100) will be recruited over 3 years, with the anticipated enrollment of 5 or more veterans per month. The desired sample size was based on a power analysis for repeated-measures ANOVA with 5 time points, α=.05, a medium effect size (f=0.25), and 80% power, plus oversampling for potential attrition (20%) estimated from studies involving patients with HF [17,18]. Veterans are eligible for participation if they (1) have a diagnosis of HF; (2) are aged 18 years or older; (3) have New York Heart Association functional class II-IV HF; and (4) can read, write, and communicate verbally in English, and excluded if they have a history of cognitive impairment.

### Data Collection

Telephone data collection is conducted by a trained research assistant who verbally asks each item and records participants’ responses in an online HIPAA (Health Insurance Portability and Accountability Act)–compliant Qualtrics database. Data are collected at baseline and 3, 6, 12, and 18 months from baseline. In addition to a sociodemographic and clinical survey (age, gender, comorbidities, education, and HF class), a set of self-report surveys is used to measure the study variables (Table 1). We also collect data on standard Veterans Administration Office of Rural Health metrics.

**Table 1 table1:** Study variables.

Variables		Baseline	3 months	6 months	12 months	18 months
**Covariates**						
	Social support	✓				
**Process**						
	Problem-solving	✓	✓	✓	✓	✓
**Outcomes**						
	HF^a^ self-care	✓	✓	✓	✓	✓
	HF symptoms	✓	✓	✓	✓	✓
	Health care utilization		✓	✓	✓	✓
	Depressive symptoms	✓	✓	✓	✓	✓
	Anxiety	✓	✓	✓	✓	✓
	HF-specific, health-related quality of life	✓	✓	✓	✓	✓
	Stress	✓	✓	✓	✓	✓
	Resilience	✓	✓	✓	✓	✓
	Coping	✓	✓	✓	✓	✓

^a^HF: heart failure.

### Study Measures

#### Social Support

The 12-item Interpersonal Support and Evaluation List measures perceived belonging, tangible, and appraisal support. The 3 subscales will be combined to obtain a single index of perceived support, in addition to the evaluation of the individual subscales. Scores range from 0-36, with higher scores suggesting a higher perception of available support [24]. Previous studies support its construct validity using the original 40-item version [24] and its internal consistency reliability (α=.90) [25].

#### Problem-Solving

The 25-item Social Problem-Solving Inventory Revised-Short measures problem orientation and problem-solving style using 5 subscales: positive and negative problem orientation, rational problem-solving, impulsivity and carelessness, and avoidance styles. The 5 subscales will be combined to provide a total score, with higher scores representing more of an adaptive problem-solving style and lower scores suggesting more of a maladaptive style. Higher scores on the individual subscales suggest more of the problem-solving characteristics [26]. Research supports its validity [16,26] and its reliability (α=.91) [25].

#### HF Self-Care

The 39-item Self-Care of Heart Failure Index v 7.2 measures HF self-care across 4 subscales: self-care maintenance, symptom perception, symptom management, and self-efficacy (α=.73-.88 across all subscales) [27,28]. Scores are standardized (0-100), with higher scores on each subscale suggesting better self-care principles. Scores ≥70 on each subscale are considered adequate; improvement of ≥8 is considered clinically significant [27].

#### HF Symptoms

HF symptoms are measured using the Heart Failure Symptom Survey. This survey contains 14 common symptoms of HF, which are rated on an 11-point scale (0–10) across 4 domains (frequency, severity, interference with activity, and interference with quality of life) based on the last 7 days. Higher scores indicate more of the respective domain in relation to the specific symptom [29]. Empirical evidence supports its content validity [29] and reliability (α=.96) [25].

#### Health Care Utilization

Health care utilization is determined by the frequency of emergency department visits and readmissions for HF and assessed via self-report. There are acceptable levels of agreement between self-report and medical record data [30].

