### Purpose, Aims, and Hypotheses

The overall purpose of this study is to adapt to the rural sociocultural context and test the efficacy of a tailored, telephone-based intervention (CARE-HF) to support the physical and mental health of rural veterans by enhancing disease self-management and coping processes. To accomplish this goal, our research aims are to:

Adapt the CARE-HF intervention content to the rural sociocultural context using findings from preliminary qualitative research.Examine the effectiveness of the CARE-HF intervention on study outcomes (HF self-care, HF symptoms, health care utilization, depressive symptoms, anxiety, health-related quality of life, stress, resilience, and coping), process (problem-solving), and antecedent (social support) in a sample of rural veterans with HF (N=100) at baseline and 3, 6, 12, and 18 months from baseline.

Our hypotheses are as follows:

Hypothesis 2a: Increases in HF self-care, health-related quality of life, resilience, coping, and problem-solving will be noted at 3 months from baseline and sustained throughout the 18-month follow-up period.Hypothesis 2b: Decreases in HF symptoms (frequency, severity, and interference with physical activity and enjoyment of life), health care utilization, depressive symptoms, anxiety, and stress will be seen at 3 months from baseline and sustained throughout the 18-month follow-up period.

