#### Main Analyses

Multilevel growth curve modeling will be used for the testing of aim 2 or the evaluation of the effectiveness of CARE-HF. For each outcome variable, a series of models will be estimated and compared using incremental fit indices, including the Akaike information criteria and the Bayesian information criteria. The first model is an intercept-only model. Then, a growth curve model with a linear growth component will be estimated. Finally, a model with a quadratic growth component will be tested. The multilevel modeling and restricted maximum likelihood estimation method will be used in R (R Foundation for Statistical Computing) [40]. This method can deal with dropouts and missing data without excluding incomplete cases. In addition to fixed effects, random effects will be estimated.

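### Health care utilization is an event count measured at four visits, but it gets the same REML growth model as the scale scores, and the protocol's only power basis does not carry over to it

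*Protocol article*

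**What the plan says.** - **Outcome.** Under Health Care Utilization: "Health care utilization is determined by the frequency of emergency department visits and readmissions for HF and assessed via self-report". Table 1 lists it among the outcomes, with ticks at 3, 6, 12 and 18 months and none at baseline.
- **Hypothesis.** Hypothesis 2b includes it among the expected decreases: "health care utilization, depressive symptoms, anxiety, and stress will be seen at 3 months from baseline", sustained to 18 months.
- **Model.** Main Analyses describes one series of growth models (intercept only, then linear, then quadratic) to be fitted for each outcome: "The multilevel modeling and restricted maximum likelihood estimation method will be used in R". No count distribution, link or exposure offset is named, and utilization is not excepted.
- **Power.** Design and Sample gives one basis: "The desired sample size was based on a power analysis for repeated-measures ANOVA with 5 time points", with "α=.05, a medium effect size (f=0.25), and 80% power", "plus oversampling for potential attrition (20%) estimated from studies involving patients with HF". It names no outcome. No event rate, dispersion or recall window for utilization appears anywhere.

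**The concern.** A linear growth model fitted by REML assumes that change adds a fixed amount per unit of time and that residual variance is constant. For event counts the variance rises with the mean and depends on the length of time covered. Effects are more naturally proportional, and a fitted straight line can fall below zero.

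The power basis has a related problem. A standardised effect f is meaningful for a scale score whose spread does not depend on its level. For a count the spread is tied to the mean, so the same f can mean a modest or an extreme reduction depending on the event rate. At stake is the reading of a non-significant utilization result. The 80% figure is the only power figure in the article, and a reader who applied it here could take a null result as evidence that CARE-HF does not affect HF events.

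**Working it through.** **1. The stated power basis.** For a one-group repeated-measures F test under sphericity, the noncentrality is n·m·f²/(1−ρ), with m visits and within-person correlation ρ. The article gives neither ρ nor a sphericity correction, so N=100 cannot be reproduced uniquely. With m=5 and f=0.25:
- ρ=0 needs 40 completers; 40/0.8 = 50 enrolled.
- ρ=0.5 needs 21 completers; 21/0.8 = 26.25, so 27 enrolled.

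With 100 enrolled and 20% attrition there are 80 completers. At ρ=0 the noncentrality is 80×5×0.0625 = 25 and power is 98.8%; it is higher at ρ=0.5. Eighty percent power is reached at f of about 0.12–0.17 with five visits and 0.13–0.19 with four. Falling short of f=0.25 therefore does not by itself mean power below 80%.

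**2. What f=0.25 means for this count.** Here f is the SD of the visit means divided by the square root of the average within-visit variance. For a count with mean μ that variance is μ + kμ², where k=0 is Poisson and k>0 allows overdispersion. Take the four planned visits and a fall that is linear in time (weights 0, 0.2, 0.6 and 1). *Example:* 0.2 events in the first interval, Poisson, every event removed by the last. The means are 0.20, 0.16, 0.08 and 0, averaging 0.11. Their SD is √(0.0236/4) = 0.0768, so f = 0.0768/√0.11 = 0.23. Even complete removal does not reach 0.25.

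For k from 0 to 2, the reduction needed to reach f=0.25 is:
- 0.2 or fewer events per interval: not attainable
- 0.3: at least 91% (not attainable at k=2)
- 0.5: 75–94%
- 1.0: 56–83%

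**3. Constant variance.** Assume counts cover the time since the last visit (3, 3, 6 and 6 months), a rate of 0.8 per year and k=1. The variance of an observed annual rate is rate/length + rate². That is 0.8/0.25 + 0.64 = 3.84 for a 3-month interval and 0.8/0.5 + 0.64 = 2.24 for a 6-month one. The variances differ with no treatment effect at all.

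**4. Simulated power on the planned visits.** *Assumptions:* 80 completers; Poisson counts with gamma frailty of variance 1; intervals as in step 3, analysed as rates with a normal-error slope; rate falling gradually from the first to the last interval; two-sided p<.05 in the direction of a decrease. The starting rates are assumed.

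| Events per veteran-year | 30% fall | 50% fall |
|---|---|---|
| 0.4 | 10% | 24% |
| 0.8 | 16% | 45% |
| 1.6 | 32% | 79% |
| 3.2 | 57% | 97% |

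Repeat runs with small differences in how the slope is timed and tested moved these figures by no more than about five points. At the top of the main range, 1.6 per year is 0.4 per 3 months, and the expected share of veterans with no event in such an interval is 1/(1+0.4) = 71%.

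**5. Gain from a count model.** For the 30% fall at 0.4, 0.8 and 1.6 per year, a paired comparison on the same simulated data gave 9%, 16% and 31% for the normal-error model and 12%, 20% and 35% for a Poisson rate model. The gain is 3 to 4 points.

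**The case against.** - **The 80% is not claimed for utilization.** This stands. Design and Sample names no outcome. A reader might infer a promise of 80% power for each outcome, but the text does not make one. The defensible statement is that no power basis for utilization exists.
- **f=0.25 out of reach does not imply low power.** This stands. A reader might infer that a medium effect is unattainable for a count and that power is therefore far below 80%. Step 1 breaks that chain, and step 2 shows that f=0.25 is attainable at higher rates with large reductions.
- **Power is not low everywhere.** This stands. A 50% fall has about 79% power at 1.6 events per year and 97% at 3.2.
- **The event rate is unknown.** This stands. Whether the HF restriction covers emergency visits as well as readmissions is also unclear, and the wider reading gives a higher rate. Sparsity is an assumption, hence the range.
- **A distribution is normally analysis-plan detail, and the article never says Gaussian.** This stands only in part. The article does not simply leave the model open: it fixes REML linear and quadratic growth for each outcome. Without a stated family or link, that is ordinarily a normal-error model.
- **The count model barely raises power.** This stands. The case for it is a suitable variance structure and an interpretable rate ratio.

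**Conclusion.** The point holds in a limited form. As written, the plan fits an additive, constant-variance growth model to an event count, and its single power basis (five time points, f=0.25) does not carry over to an outcome scheduled at four visits. The first part follows from the text, given the ordinary meaning of REML growth modelling.

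The size of the power shortfall rests on assumed event rates, frailty variance 1, 80 completers and counts that run from visit to visit. On those assumptions power is roughly 10–32% for a gradual 30% fall and 24–79% for a 50% fall at 0.4 to 1.6 events per veteran-year. It is therefore low for modest reductions or low rates, and adequate only when both are large. The documents do not support saying that power is far below 80% in general.

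The missing baseline measurement of utilization is a separate matter. Adding one would not make a normal-error model suitable for the count.

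**What to change.** - **Main Analyses:** take utilization out of the REML growth series. Analyse it with a Poisson or negative binomial mixed model, or the GEE equivalent, with the length of the interval covered by each count as offset. Report a rate ratio with its 95% confidence interval. The interval that each self-reported count covers must be stated for the offset to be right.
- **Design and Sample:** say that the f=0.25, 80% power statement refers to the continuous scale scores and not to utilization, and that a non-significant utilization result will be read from its confidence interval and not as absence of effect.

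**Cost:** one extra model type in R and a less favourable power statement for one outcome. No added veterans and no new outcome measure. The Results section places data analysis after study completion, so the change can be made beforehand. It should not be presented as a remedy for low power, since the gain at a 30% fall is only about 3 to 4 points.

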#### Depressive Symptoms

Depressive symptoms are measured using the 20-item Center for Epidemiological Studies—Depression Scale. Overall scores range from 0 to 60, with higher scores indicating the presence of more depressive symptoms. A cutoff score of 16 indicates an individual is at risk for some degree of depression. Previous studies support its validity (Radloff [31]) and reliability (α=.90) [25].

#### Anxiety

The Generalized Anxiety Disorder-7 scale is a valid and reliable (α=.92) 7-item scale that assesses the presence of anxious symptoms over the past 14 days, using a Likert scale to rate the frequency of the symptoms (0=not at all, 1=several days, 2=more than half of the days, and 3=nearly every day). Total scores range from 0 to 21, with higher scores indicating more severe anxiety symptomatology [32]. In this study, the following recommended anxiety severity categories will be used: none or normal (0-4), mild (5-9), moderate (10-14), and severe (15-21) [32].

#### Health-Related Quality of Life

The multidimensional 21-item Minnesota Living with Heart Failure Questionnaire measures the physical, socioeconomic, and emotional dimensions of HF-specific, health-related quality of life. This self-report survey asks respondents to evaluate the way they have felt in relation to the specific dimension over the last 4 weeks. Scores for the individual dimensions, as well as a total score, are obtained by summing the individual items. Higher scores suggest worse health-related quality of life relative to the specific dimension or overall. A change of ≥5 points is considered clinically meaningful [33]. Previous studies support its validity [33] and reliability (α>or=.80 across dimensions) [34].

#### Stress

The valid and reliable 10-item Perceived Stress Scale measures stress and includes questions relative to feelings and thoughts experienced during the last month using a Likert scale with scores ranging from 0 (never) to 4 (very often). Higher scores indicate higher levels of acute stress [35].

#### Resilience

The 25-item Five-by-Five Resilience Scale has 5 subscales that measure adaptability, emotion regulation, optimism, self-efficacy, and social support on a 5-point Likert scale (1=very inaccurate to 5=very accurate). Higher scores represent higher levels of resilience relative to the specific facet. Previous research shows adequate validity and reliability (α=.81-.93 across subscales) [36].

#### Coping

The Brief Coping Orientation to Problems Experienced is a 28-item scale that measures 14 coping strategies over 3 subscales (active emotional coping, avoidant emotional coping, and problem-focused coping) on a 4-point scale ranging from 1 (I haven’t been doing this at all) to 4 (I have been doing this a lot). Higher scores on the subscales suggest more use of the specific type of coping strategy [37]. Previous research has indicated the measure is valid [37] and reliable (α=.78) [38].

### Procedure and Intervention

#### CARE-HF

Veterans are trained to use social problem-solving skills to manage common HF-related problems in the home during 8 telephone sessions led by a trained registered nurse interventionist (NI).

#### Initial Telephone Session

Before the first session, veterans are mailed program materials and a manual presented at a sixth-grade reading level. To start the first telephone session, participants receive an overview of the program manual, tailored to the rural context, which includes information about social problem-solving principles. The manual also includes detailed real-life examples drawn from the rural setting of how to use the five-step, problem-solving process to evaluate and manage HF-related problems based on previous research (Table 2) [8]. Each example includes a positive problem-orientation approach and rational problem-solving strategies to address these HF-related problems. The NI uses fatigue as an example when discussing how to apply the iterative five-step, problem-solving process to manage actual HF-related problems. The five-step, problem-solving process is based upon the “Theory of Social Problem-Solving” and rational problem-solving principles and includes (1) identifying the problem and viewing it in a positive manner, (2) setting a goal related to problem management, (3) generating potential strategies to address the problem, (4) choosing and implementing one to two strategies to manage the problem, and (5) evaluating the effectiveness of chosen strategies [16].

Veterans are then asked to participate in a card-sorting task. Veterans are given a set of cards portraying HF-related problems identified in previous research (Table 2) [8,12] and asked to prioritize the cards from the highest priority problem to the lowest. Then, the NI will guide veterans in applying the problem-solving process to the HF-related problem identified as the highest priority. Next, the NI describes the benefits of reframing the problem in a positive manner and facilitates the selection of preliminary strategies to manage them. In doing so, the NI explores through discussion with the participants how their values and beliefs can be incorporated into potential strategies. Participants then choose one to two strategies on which to focus, the results of which are reviewed at the next session. The five-step, problem-solving process is reinforced throughout the intervention period in the follow-up telephone sessions.

**Table 2 table2:** HF^a^-related problems and examples.

Problem categories	Examples
Monitoring and managing HF symptoms	Fatigue (tiredness) Forgetfulness Edema (swelling) Activity intolerance Difficulty breathing (shortness of breath)
Staying on your special diet program	Access to suitable foods Shopping for and cooking correct foods Limiting fluids (if recommended) Barriers to eating foods with less salt Personal food likes and dislikes Not sure how to read and understand food labels
Staying on your HF treatment program	Take daily weights Exercise regularly (as recommended) Keep regular health care visits Get immunizations (flu, RSV^b^, pneumonia, and COVID-19) Use oxygen (as directed) Stop smoking
Dealing with unhelpful emotions	Sadness Anxiety Decreased quality of life Depression Anger Negative life changes
Social isolation and loneliness	Unable to do normal activities (community, church, family, and friends) Fewer or no invitations to social events with friends and family Feeling as if you have no one to turn to for support Feeling alone
Medicine management	Difficulty in obtaining medicine Unable to pay for medicine Problems in preparing medicine Trouble in taking medicine on time Taking several medicines for other health problems
Health beliefs	How you view your health and wellness (accept, do not accept, positive, or negative) How well you think you can do health activities for yourself (good, ok, or not well) Your view of how well the heart medicine and treatment works (works well, no change, or does not help)
Caring for yourself (self-autonomy)	You want to do everything for yourself and or make health care decisions whether you can or not Family or friends want to do everything for you and or make health care decisions whether you can or not
Social support and community resources	Family or friends who live close by Church members and social group friends Neighbors Local senior center Home health Grocery store or grocery delivery programs nearby Food pantry Pharmacy nearby Public transportation
Managing HF and other health issues	Managing HF and: Diabetes Neurological disorders

^a^HF: heart failure.

^b^RSV: respiratory syncytial virus.

